### Sample size determination

The power analysis must take into account potential clustering effects due to unit, as well as IC within the Online+MS-BPD arm [34]. The average number of participants per unit is 1.5 (*m*_*H*_). The responses of members from within the same unit might be more alike than responses between different units. It is difficult to estimate the magnitude of likely intraclass correlations but substantial effects must be considered, thus, the intraclass correlation coefficient was conservatively estimated to be at 0.2 (*ρ*_*εθ*_).

It is recognised that receiving the Online+MS-BPD intervention in a group setting might result in participants’ responses being more alike within each round than between rounds. This might arise due to effects associated with each round’s facilitators, along with events, experiences and relationships that emerge at each round. However, in the case of psychoeducation interventions, clustering effects are typically very low. This is due to the absence of any pre-existing clustering (in contrast to clustered RCTs), the programmatic nature of the intervention, and the limited amount of interaction participants have within the rounds. As such, we conservatively estimated the IC to be correlated at 0.03 (*ρ*_*θT*_). Our pilot data revealed that the average number of participants per MS-BPD round was 9.4 (*J*). Using these parameters, the maximum design effect would be 1.24.

Taking the above factors into account and assuming a correlation of 0.5 between baseline and outcome measures, a total sample of 54 units would have power of 80% to detect a difference of 0.5 standard deviations between the Online and Online+MS-BPD arms. This effect size is regarded as a medium size difference.

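### The stated 80% power for 0.5 SD with 54 units in total does not follow from the protocol's own inputs; with alpha assumed two-sided 5% and baseline adjustment it is about 65%

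*Protocol article*

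**What the plan says.** The Sample size determination section of the protocol article builds its figure in three steps.

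- Clustering by family unit: "The average number of participants per unit is 1.5", and "the intraclass correlation coefficient was conservatively estimated to be at 0.2".
- Clustering by MS-BPD round, in the combined arm only: "we conservatively estimated the IC to be correlated at 0.03", with an average of 9.4 participants per round. The section then says: "Using these parameters, the maximum design effect would be 1.24".
- Power: with these factors included, and "assuming a correlation of 0.5 between baseline and outcome measures", the section concludes that "a total sample of 54 units would have power of 80% to detect a difference of 0.5 standard deviations".

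The Randomisation and blinding section gives 1:1 allocation. The section on sample size gives no alpha or sidedness and no formula for using the baseline correlation. The Statistical analysis section plans mixed models with unit and round as random factors, extended with baseline and other covariates. It does not say whether the primary contrast is a baseline-adjusted week-seven difference or a difference in change.

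**The concern.** Apart from alpha, the section gives enough to recompute the power, and the standard formulas return a clearly lower figure than 80%. This is the article's only justification of the trial's size. Readers will take the trial as an 80% test of a medium effect. If power is nearer 65%, a true benefit of 0.5 SD is missed about one time in three. The Discussion considers what a finding of no added benefit from MS-BPD might mean. Its reading is cautious and claims no equivalence, but the weight a reader gives to a null result still depends on the stated power.

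**Working it through.** **Inputs.** From Sample size determination: 54 units in total, 1.5 carers per unit, design effect 1.24 (called a maximum), r = 0.5, difference 0.5 SD. From Randomisation and blinding: 1:1. Assumed, because not stated: two-sided 5%, with one-sided 5% shown as a variant because the hypothesis in the Background is directional. No loss to follow-up is applied.

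**Carers.** 54 × 1.5 = 81, or 40.5 per arm.

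**Design effect by arm.** The stated 1.24 is applied to both arms first. Round clustering exists only in the Online+MS-BPD arm, so a kinder version uses unit clustering alone for Online: 1 + (1.5 − 1) × 0.2 = 1.10, with 1.24 for Online+MS-BPD.

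**Variance factor from r = 0.5.** Baseline-adjusted: 1 − r² = 0.75. Change score: 2(1 − r) = 1.00. An analysis that ignores baseline also has factor 1.00.

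**Formula.** SE = √[factor × (DE for Online + DE for Online+MS-BPD) / 40.5]. Power = Φ(0.5/SE − z), with z = 1.96 (two-sided) or 1.645 (one-sided). The difference detectable with 80% power, two-sided, is 2.80 × SE.

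**Main case worked through.** SE = √(0.75 × 2.48 / 40.5) = 0.2143. Then 0.5/0.2143 = 2.333, and Φ(2.333 − 1.96) = 0.645. A t-based version gives about 63%. The detectable difference is 2.80 × 0.2143 = 0.60 SD.

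| Variance factor | DE Online / Online+MS-BPD | Power, two-sided 5% | Power, one-sided 5% | 80%-power difference, two-sided |
|---|---|---|---|---|
| 0.75 (baseline-adjusted) | 1.24 / 1.24 | 64.5% | 75.4% | 0.600 SD |
| 0.75 | 1.10 / 1.24 | 67.1% | 77.5% | 0.583 SD |
| 1.00 (change score) | 1.24 / 1.24 | 52.4% | 64.6% | 0.693 SD |
| 1.00 | 1.10 / 1.24 | 54.8% | 66.8% | 0.673 SD |

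No row reaches 80%.

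**Trying to reproduce the stated 80%.** Several routes come close, and each departs from what the section says.

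- 54 units per arm (81 carers per arm) with change scores, two-sided: SE = √(2.48/81) = 0.175; 0.5/0.175 = 2.857; Φ(0.897) = 81.5%. This contradicts the description of 54 as a total.
- 54 units in total with a variance factor of 0.5, two-sided: SE = √(0.5 × 2.48/40.5) = 0.175, so again 81.5%. A factor of 0.5 is not the variance of either standard analysis at r = 0.5.
- One-sided 5%, baseline-adjusted, with 1.10 in both arms: 79.7%. This leaves out the round effect.
- One-sided 5%, baseline-adjusted, with 1.0 for Online and 1.24 for Online+MS-BPD: 79.1%. This leaves out unit clustering in the Online arm.
- A correlation of about 0.7 instead of 0.5, two-sided with 1.24, baseline-adjusted: 80.8%.

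**Size of the gap in units.** Two-sided 5% with 1.24 in both arms, 80% power for 0.5 SD corresponds to 58.4 carers per arm when baseline-adjusted: 2 × 58.4 / 1.5 = 77.9, about 78 units. With change scores it is 77.9 carers per arm: 2 × 77.9 / 1.5 = 103.9, about 104 units.

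**The case against.** The strongest reply is that the 65% is conditional. Alpha is the reviewer's assumption, the hypothesis is directional, and 1.24 is described as a maximum while round clustering affects one arm only. With one-sided 5%, baseline adjustment and 1.10/1.24, power is 77.5% and the difference detectable with 80% power is about 0.52 SD, which is close to the claim. The calculation also follows a cited methods paper on partially nested designs that is not available here. All of this stands as a reason to give a range with its conditions, but none of it brings the figure to 80% with both clustering sources included.

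Four stronger readings are tempting and are not supported.

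- *The authors used a variance factor of (1 − r).* No variance factor appears in the article, and 54 per arm with change scores gives the same 81.5%. The text cannot separate the two.
- *The trial is underpowered.* That follows only if 54 really is the total. If it was meant per arm, power at two-sided 5% is 82% with change scores or 91% with baseline adjustment.
- *The claim fails even with no clustering at all.* At two-sided 5% with baseline adjustment it does (73.8%). At one-sided 5% it does not (83.0%).
- *Dropout lowers power further by a known amount.* The article gives no loss rate and expects little missing data, and any allowance may sit in the full protocol.

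**Conclusion.** The stated power does not follow from the stated inputs, and the sentence is wrong as written. With 54 units as the total, two-sided 5% and baseline adjustment, power for 0.5 SD is about 65% (67% with arm-specific design effects), and 80% power belongs to a difference of about 0.58 to 0.60 SD. Change scores give about 52 to 55%. One-sided 5% with baseline adjustment gives about 75 to 78%. The specific percentages rest on the assumed alpha and on the choice of analysis. The failure to reach 80% does not: it holds for every standard analysis tried, one- or two-sided at 5%, that includes both unit and round clustering with 54 units in total. Whether the slip is in the power or in the label of the 54 cannot be settled from the article.

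**What to change.** Check the original calculation, then restate the sentence with alpha, sidedness and the analysis to which the power refers.

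- If 54 is the total, write for example: *54 units in total (about 81 carers) give about 65% power for 0.5 SD, or 80% power for about 0.60 SD (two-sided 5%, baseline-adjusted).* This is a one-paragraph rewording. The stated power becomes less favourable, and the restatement needs no extra carers.
- If 54 was meant per arm, replace the total by 54 units per arm (108 units) and give the matching power at two-sided 5%: 82% with change scores or 91% with baseline adjustment. The edit is equally short, but the stated recruitment target then doubles, so this must be settled against the sponsor's own calculation.

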## Discussion

To the authors’ knowledge, this will be the first published RCT of any psychoeducational program for carers of youth with BPD. We have designed and previously empirically tested MS-BPD, the first psychoeducational group program for carers of youth with BPD features, that places BPD in an appropriate development context and addresses the needs of carers of youth, early in the course of the disorder [19]. By employing an RCT design and an ‘active’ comparison condition, this study will allow for a more rigorous test of the effectiveness of MS-BPD, compared with an online BPD program with a focus on psychoeducation.

The trial’s findings will help to clarify the extent to which psychoeducational programs for carers of youth with BPD features are effective, and to give feedback about their content. If the online program is found to be effective then it can be readily applied in clinical practice. The program only requires carers to have internet access, is of short duration, can be accessed multiple times, and can be completed in stages. These elements are likely to make the online program attractive to carers who are busy juggling a range of family, study and work commitments. It is also a low-intensity intervention for services to offer, a key issue in the utilisation of carer interventions [36]. If the trial finds that the online program is not effective, it might be that the design, content, or length of the program needs revision or that group processes are key in contributing to change.

If the combination of the online program and MS-BPD proves to be most effective, then this supports the implementation of more resource-intensive interventions, requiring a relatively greater investment by both carers (in attending an on-site group) and services (using specialist clinicians and family peer support workers in conducting the group). However, and importantly for uptake, specialist psychotherapy training (in CAT) is not required of those conducting the group. The manualised MS-BPD program, with its standardised materials, can easily be disseminated for use in a range of clinical settings. Factors that might be responsible for the combined Online+MS-BPD intervention being more effective might include: (i) validation of and connection with the experiences of other carers; (ii) shared problem solving; (iii) the opportunity to ask questions and to discuss or tailor the content to individual circumstances; and (iv) facilitators’ capacity to respond to dynamic group needs, depending upon how the material is understood or the feelings being expressed within the group. The specific effect of each factor or MS-BPD component has not been evaluated, but would be of interest for future research. If offering MS-BPD in addition to the online program does not improve outcomes over and above Online, then it might be that MS-BPD is more effective for carers with greater difficulties (e.g., higher levels of burden and distress), whereas the less intensive online program might be sufficient for carers experiencing fewer difficulties.

While this trial’s design attempted to overcome problems identified in previous studies, there are some anticipated limitations. This trial will not assess the maintenance of any changes over the medium- to long-term. Future studies would be strengthened by having additional follow-up assessments, longer than four to eight weeks post-intervention. Compared with participants in the Online arm, participants in the Online+MS-BPD arm might have greater exposure to psychoeducation, given that they will have the Online material repeated by MS-BPD facilitators. The trial results will therefore need to be interpreted with this in mind, with the Online usage data and MS-BPD attendance rates elucidating whether the ‘dose’ of psychoeducation differed between the trial’s arms. Further, reflective of ‘real-world’ clinical practice, carers are free to access additional carer-specific resources, which might confound the trial’s findings. OYH, for example, offers individual sessions with specialist family clinicians and peer support from trained family peer support workers. However, data on the use of such resources is being collected and will be controlled for in our analyses. Although beyond the scope of this trial, if the online program and MS-BPD prove to be effective for carers, an examination of whether improved carer outcomes might be associated with better outcomes for young people with BPD is warranted. To the authors’ knowledge, this relationship has not previously been empirically tested and will be an important extension of the field.

Notwithstanding these limitations, the trial design has several strengths. The trial benefits from broad inclusion criteria, with few exclusion criteria, which enables the recruitment of a sample that reflects the clients and carers who present to government-funded specialist mental health services in Melbourne, Australia. Carers representing a range of different types of relationships are included, rather than limiting the study to just parents, or mothers, as is commonly the case [7]. While much of the research to date has focused on those caring for females with BPD, this trial includes carers of both males and females with BPD [7]. BPD is assessed with a standardised clinical interview. Lastly, the manualised nature of MS-BPD and the pre-programmed MS-BPD and Online resources ensure treatment integrity.

In conclusion, this trial will test the effectiveness of an online psychoeducation intervention for carers of youth with BPD, alone or in combination with a face-to-face psychoeducation group. Results will have the potential to inform clinical decisions about which program, or combination of programs, to offer carers of youth with BPD features, as well as enabling carers to choose the style of intervention that best suits their needs.

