### Outcome measures

The primary outcome is burden, defined as the combined total score of negative appraisal subscales of the Experiences of Caregiving Inventory (ECI; [24]). The secondary outcomes include positive experience of caregiving (ECI total positive appraisal subscale; [24]), coping (Coping Inventory for Stressful Situations; [25]), self-rated personality disorder knowledge (selected items from Personality Disorder Knowledge, Attitudes and Skills Questionnaire, modified for use with carers; [26]), distress (Kessler Psychological Distress Scale; [27]), expressed emotion (Family Questionnaire; [28]), and quality of life (Assessment of Quality of Life - 8 Dimensions and Quality of Life Enjoyment and Satisfaction Questionnaire - Short Form; [29, 30]). Subsidiary measures capture demographic, treatment/resource use and diagnostic information (e.g. Structured Clinical Interview for Diagnostic and Statistical Manual of Mental Disorders, Fourth Edition, Axis I and II disorders; [31, 32]). Table 1 lists the trial measures.

**Table 1 Tab1:** Schedule of outcome measures

	Time point	
Measure	Baseline	Week Seven
*Primary Outcomes*		
Combined total negative appraisal subscales of the Experience of Caregiving Inventory (ECI)	✔	✔
*Secondary Outcomes*		
Combined total positive appraisal subscales of the ECI	✔	✔
Coping Inventory for Stressful Situations (CISS)	✔	✔
Personality Disorder Knowledge Attitudes and Skills Questionnaire (PDKASQ) ^a^	✔	✔
Kessler Psychological Distress Scale (K-10)	✔	✔
Family Questionnaire (FQ)	✔	✔
Assessment of Quality of Life (AQoL-8D)	✔	✔
Quality of Life Enjoyment and Satisfaction Questionnaire – Short Form (Q-LES-Q-SF)	✔	✔
*Subsidiary Measures*		
Demographics - carers	✔	✔
Carer-specific Resource Use	✔	✔
Demographics – clients ^b^	✔	
Treatment Data ^b^		✔
SCID-II Personality Questionnaire for BPD ^b^	✔	
Diagnosis DSM-IV SCID-I/P ^b^	✔	
BPD diagnosis DSM-IV SCID-II ^b^	✔	

aThree items, modified for use with carers rather than clinicians

b Measures completed with clients, not carers

*BPD* borderline personality disorder, *DSM-IV* Diagnostic and Statistical Manual, Fourth Edition, *SCID* Structured Clinical Interview for DSM-IV; SCID-I/P=SCID Axis I Disorders, Patient Version; SCID-II=SCID Axis II Disorders

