### Procedure

Participants (and a parent/legal guardian for minors) are asked to provide written informed consent. A carer’s participation is not dependent on their young person also consenting to participate. Carers who decline participation in the trial may still utilise the interventions. The interventions are delivered in rounds, approximately every 12 weeks. Information collected as part of routine clinical care [33] is extracted from consenting clients’ medical records. Carers are given baseline questionnaires up to 2 weeks prior to the forthcoming round, and upon completion of these, carers are randomly and consecutively assigned to the next Online or Online+MS-BPD as a family unit. Follow-up questionnaires are issued at week seven, (4 weeks after the intervention), and carers have up to 4 weeks to complete these. The baseline and follow-up questionnaires are self-rated, online or in hard copy. Figure 1 shows the participant flow chart.

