### Statistical analysis

The analysis will be by intention-to-treat. Two sources of potential non-independence (clustering) of observations are: (1) participation in the intervention by more than one carer associated with an individual client (a ‘unit’); (2) the round of MS-BPD attended. Thus, the unit is considered a cluster and within the Online+MS-BPD arm, the MS-BPD round attended is considered the intervention cluster (IC). Such a design is referred to as a partially nested, clustered RCT [34]. To accommodate this design, mixed models will be used with unit and IC fitted as random factors [34]. Although low levels of missing data are expected, mixed models have the advantage of retaining the observations of participants who have missing data [35]. The models will be extended to include baseline and time varying covariates as well as categorical variables that might confound outcomes and require adjustment. A two-step approach will first identify individually significant and near-significant associations with outcome measures, and then simultaneously fit these variables in a multiple predictor model. This approach will be applied to each of the outcomes specified in the hypotheses. Adaptations of this approach will be used to explore predictors of the outcomes. Further, given that mothers have been the most frequent attendees of MS-BPD to date, exploratory analyses of this subgroup alone will occur. It is recognised that these analyses will have reduced power to detect change and the study has not been powered for subgroup analyses.

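### Controlling for carers' use of other support after randomisation may distort the arm comparison, and the protocol does not say that a model without it is decisive

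*Protocol article*

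**What the plan says.** The relevant statements are spread over several sections of the protocol article.

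- **Statistical analysis.** The governing principle is stated first: "The analysis will be by intention-to-treat". Mixed models with unit and intervention cluster as random factors follow. Then: "The models will be extended to include baseline and time varying covariates as well as categorical variables that might confound outcomes and require adjustment". Selection is by association with outcome: "A two-step approach will first identify individually significant and near-significant associations with outcome measures". The variables that pass are then fitted together. On scope: "This approach will be applied to each of the outcomes specified in the hypotheses". The hypotheses at the end of the Background include carer burden, the primary outcome.
- **Discussion, limitations paragraph.** The reason for adjusting is that "carers are free to access additional carer-specific resources, which might confound the trial’s findings". Individual sessions with family clinicians and peer support are the examples given. The commitment follows: "However, data on the use of such resources is being collected and will be controlled for in our analyses".
- **Outcome measures, Table 1.** "Carer-specific Resource Use" is scheduled at baseline and at week seven.
- **Procedure.** Carers complete the baseline questionnaires and, "upon completion of these, carers are randomly and consecutively assigned to the next Online or Online+MS-BPD as a family unit".

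**The concern.** A confounder of the arm comparison has to be associated with allocation other than by being caused by it. Randomisation rules that out, apart from chance imbalance in variables that already exist at allocation. Support that carers take up after allocation is a different kind of variable, because allocation can change it.

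The protocol makes such a change plausible. Under Randomisation and blinding, carers and clinicians know the arm. Under Interventions, the group is run by specialist clinicians and its third session is co-facilitated by a family peer support worker. Peer support is itself one of the outside resources to be controlled for. Attending the group could therefore prompt more use of such services or replace some of it.

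What is at stake is the meaning of the arm coefficient. The trial is meant to inform which programme to offer carers, and that calls for the total effect of offering the group in addition to the online program. If allocation shifts resource use, a model that holds use fixed estimates something else. Screening on association with outcome does not guard against this. It favours variables on the path to the outcome, and variables that respond to burden. Week-seven resource use is recorded at the same assessment as the outcome.

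**Working it through.** **Step 1: is the variable measured before or after randomisation?** Randomisation follows the baseline questionnaires (Procedure). Table 1 gives two resource-use values, so the baseline value precedes randomisation and the week-seven value follows it. The limitations paragraph is about services that carers are free to use while the trial runs, which the baseline value cannot capture. The Statistical analysis section also refers to time-varying covariates. The natural reading is therefore the week-seven value.

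**Step 2: does any passage contain the problem?** No passage restricts the adjustment to baseline values, calls it a sensitivity or exploratory analysis, or names an unadjusted or baseline-only model as the one that decides the hypotheses.

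**Step 3: size.** The protocol has no figure of its own to reproduce here. Two of its values are used: the target difference of 0.5 SD and the baseline-outcome correlation of 0.5 (Sample size determination). Everything else below is assumed. Lower burden is better, so the true total effect is set at −0.50 SD.

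Let *a* be the effect of allocation on resource use (in SD) and γ the coefficient of resource use in the model that also contains arm and baseline burden. For linear models:

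adjusted effect = total effect − *a* × γ

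*Mediation only.* Use lowers burden by 0.2 SD per SD (γ = −0.2), with no unmeasured common cause.

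| *a* | −*a* × γ | Adjusted effect |
|---|---|---|
| +0.50 | +0.10 | −0.40 |
| +0.25 | +0.05 | −0.45 |
| 0 | 0 | −0.50 |
| −0.25 | −0.05 | −0.55 |
| −0.50 | −0.10 | −0.60 |

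If the group raises use of helpful services, adjustment shrinks the estimate. If the group replaces such use, adjustment enlarges it.

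*Collider only.* Use has no effect on burden, but an unmeasured severity factor loads 0.3 on use and 0.4 on burden and correlates 0.5 with baseline burden. After conditioning on baseline burden, the variance of that factor is 1 − 0.5² = 0.75. Then:

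γ = (0.3 × 0.4 × 0.75) / (0.3² × 0.75 + 1 − 0.3²) = 0.09 / 0.9775 = 0.092

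At *a* = +0.5 the shift is −0.046, giving about −0.55. At *a* = −0.5 it is +0.046, giving about −0.45. At *a* = ±0.25 it is 0.023 in size. The signs are opposite to those under mediation.

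*Both together.* γ = −0.2 + 0.092 = −0.108, so the shift is 0.054 in size at *a* = ±0.5 and 0.027 at *a* = ±0.25.

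A least-squares simulation of 500,000 observations per scenario agreed. Mediation gave shifts of 0.10 at *a* = ±0.5, the collider case gave 0.046, and the combined case 0.054. The shift was zero, to within 0.001, whenever *a* = 0.

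**Step 4: relative size.** 0.05 / 0.5 = 10% and 0.10 / 0.5 = 20% of the target difference. At *a* = ±0.25 the three cases give 0.02 to 0.05 SD.

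**Step 5: effect on the design.** The sample size calculation takes credit only for the baseline-outcome correlation. Dropping post-randomisation covariates leaves it unchanged.

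**The case against.** The strongest reply has four parts.

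1. *The models are extended, so a simpler model comes first.* This is fair. The text does not call the covariate-extended model primary, and a reader who infers that the primary model is committed to resource use goes beyond it. But neither is the simpler model named as decisive, and the covariate approach is applied to every hypothesised outcome. An analysis plan that is not shown might settle the matter. The article's own commitment to control for resource use would still need to be reconciled with it.

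2. *The commitment sits in a limitations paragraph and names no model or time point.* Adjusting for baseline use would be sound. However, the baseline value does not answer the concern that the paragraph raises.

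3. *Bias is conditional.* A reader might infer that the adjustment is bound to bias the result. The documents do not support that. Nothing in them reports an effect of arm on resource use, and without one there is no bias. The collider path also needs an arm effect on use and a common cause that remains after baseline adjustment. That worse-off carers seek more help is not enough alone.

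4. *Intention-to-treat is not abandoned.* This is correct as to who is analysed. Covariates do not move carers between arms, and Discontinuation and withdrawal keeps withdrawn carers in the sample. What may be lost is the total effect that such an analysis is normally meant to estimate.

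A reader might also infer a much larger distortion. A shift of 0.20 SD, 40% of the target, needs *a* = 0.5 together with γ of size 0.4. The first is an effect on service use as large as the target effect on burden. Nothing in the documents supports that pair.

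**Conclusion.** The point holds in conditional form. As written, the protocol allows week-seven resource use, and other time-varying covariates chosen by association with outcome, into the models for all hypothesised outcomes, and it describes a possible consequence of allocation as a confounder. If allocation changes resource use, the adjusted arm coefficient may differ from the total effect.

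Size and direction are unknown. Under the assumed values the shift is about 0.05 to 0.10 SD at an arm effect on use of ±0.5 SD, roughly half that at ±0.25 SD, and zero if there is no arm effect. These figures rest on linear models and on assumed values for the effect of arm on use, the effect of use on burden, and the strength of any unmeasured common cause. They illustrate the problem and do not estimate what this trial will show.

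This should be fixed before analysis, because it reaches the primary outcome and the remedy is simple. It does not invalidate the design.

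**What to change.** In Statistical analysis, state that the hypothesis tests use the mixed model adjusted only for variables measured before randomisation, for example baseline score, the stratification factors and baseline resource use. Exclude from that model week-seven resource use and any other time-varying covariate that allocation could affect. A covariate that allocation cannot influence need not be barred.

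In the Discussion, replace the commitment to control for resource use with a commitment to report week-seven use by arm, and label any model that adjusts for it as exploratory.

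The cost is a few sentences of wording. Table 1 already schedules both resource-use measurements, so no new data are needed, and the sample size calculation is untouched.
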